## Methods and analysis

### Study design

In order to answer the research questions, outcome, process and health economic analyses will be carried out. Different research methods will be used for this purpose. The comparative population will be formed by randomising the groups of participants. The division into the respective groups (intervention group, IG or control group, CG) will be carried out monthly to ensure that the patients of both groups are not able to exchange information with each other. Patients who start an MPT simultaneously in the Rehabilitation Center each form a cluster. These clusters will be randomised to the IG or CG (see figure 2). The evaluator will inform the Rehabilitation Center monthly via email in the third week of the MPT whether the group is an IG or CG. Up to this point, neither the patient nor the treatment staff will know which group the patient belongs to. The recruitment period will be 24 months.

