### Sample size calculation

The case number calculation was carried out for the primary outcome days of incapacity to work. Currently, the described patient group of AOK-insured persons has an average number of 37 days off work (SD: 58) per year. It is assumed that the average number of 37 days off work per year will decrease in the IG by 40% (or 15 days) compared with the CG. This results in an effect size of d=0.3409275. To test with a power of 80% (1−ß=0.8) and a significance level of 5% (ɑ error=0.05), a case number of 137 subjects per group is required for significant proof of the expected effect. The number of cases was calculated using the software G*Power (see online supplemental figureS2).

Taking an intraclass correlation coefficient of 0.01 and a design effect of 1.1 at an average cluster size of 15.3 (22×16+2×8) into account, the required number of cases is 293 subjects, that is, 147 subjects per group.^29–32^ Considering a drop-out of 10% for patients who drop out during the MPT, that is, before randomisation, results in a required total case number of 322. The available population covers the required case number (see figure 3 and online supplemental figure S2).

10.1136/bmjopen-2022-067412.supp2Supplementary data

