#### Primary outcome

The data will be analysed by reference to the primary outcome (days of incapacity to work), which is carried out by intention-to-treat analysis. Patients are analysed according to their original group assignment.

To test the primary hypothesis H_1_ ‘The intervention reduces the number of days of incapacity to work’, an analysis of covariances with cluster adjustment will be performed, using a significance level of 0.05. Covariables included into the model will be age, gender and comorbidities (eg, depression). In addition, a hypothesis test (two-sided t-test with a significance level of 0.05) will be performed.

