#### Secondary outcomes

Data for secondary outcome variables will be obtained via questionnaires and claims data. The Markov Chain Monte Carlo approach in SPSS (Version 28) will be used as imputation method to replace missing values.^34–36^ To test the hypothesis H_2_ ‘The intervention increases functional capacity’ and H_4_ ‘The intervention reduces direct and indirect costs’, hypothesis tests (two-sided t-test with a significance level of 0.05) will be performed. The third hypothesis H_3_ ‘The intervention is perceived positively by the participating patients’ will be tested by conducting a pencil–paper questionnaire with the patients. The analyses are carried out using the software programme SPSS (Version 28).

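### Functional capacity (H2) and costs (H4) are to be compared by two-sided t-tests with no cluster adjustment, although monthly clusters are randomised; the extra t-test for H1 needs a label

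*Protocol article*

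**What the plan says.** All references are to the protocol article.

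- **Study design:** "Patients who start an MPT simultaneously in the Rehabilitation Center each form a cluster", and "These clusters will be randomised to the IG or CG". Recruitment lasts 24 months, so there are about 24 clusters.
- **Sample size calculation:** the number of patients is inflated using an "intraclass correlation coefficient of 0.01 and a design effect of 1.1 at an average cluster size of 15.3". This calculation is stated to be for the primary outcome.
- **Primary outcome:** H1 is tested by an analysis of covariance with cluster adjustment at 0.05. The text then adds: "In addition, a hypothesis test (two-sided t-test with a significance level of 0.05) will be performed".
- **Secondary outcomes:** for H2 and H4, "hypothesis tests (two-sided t-test with a significance level of 0.05) will be performed". Clustering is not mentioned there.
- **Statistical analysis:** the H4 test was changed from one-sided to two-sided. It was therefore reconsidered and remained a t-test.

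**The concern.** An ordinary two-sample t-test assumes independent patients. Here patients who start together are allocated together and treated in the same small groups. The sample size section accepts that their outcomes may be correlated. With positive correlation, the between-arm difference varies more than the t-test's standard error allows.

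Two conclusions depend on this. The protocol frames H2 as a significance claim at p<0.05 (Outcome evaluation), and H4 carries the claim of lower costs. Both could be declared significant more often than the stated 5% under no effect.

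For H1 the issue is smaller. A second test at the same level stands beside the cluster-adjusted one without being called supplementary or descriptive.

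**Working it through.** **Inputs from the protocol**

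- Clusters: 22 months of 16 patients and 2 of 8, that is 352 + 16 = 368 patients in 24 clusters.
- Mean cluster size: m = 368/24 = 15.33. With the 293 patients required, m = 293/24 = 12.2.
- ICC: 0.01, given for the primary outcome only.

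**Input assumed:** an ICC for functional capacity and costs. None is given, so I take 0.01 (borrowed from the primary outcome), 0.02 and 0.05.

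**The plan's own figures.** "This results in an effect size of d=0.3409275"; at two-sided 0.05 and 80% power, the t-test calculation gives 136.02, rounded up to the stated 137 per group. The design effect is DE = 1 + (m − 1) × ICC = 1 + 14.33 × 0.01 = 1.143, which the protocol rounds to 1.1.

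**Size of a t-test that ignores clusters.** The true variance of the difference is DE times the one assumed, so

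- true two-sided size = 2 × [1 − Φ(1.96/√DE)]
- relative shortfall in interval width = 1 − 1/√DE

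At ICC 0.01 and m = 15.33: 1.96/√1.143 = 1.833, so the size is 0.067 and the shortfall is 1 − 1/1.069 = 6.5%.

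| ICC | m | DE | True size at nominal 5% | Interval too narrow by |
|---|---|---|---|---|
| 0.01 | 12.2 | 1.112 | 6.3% | 5.2% |
| 0.01 | 15.33 | 1.143 | 6.7% | 6.5% |
| 0.02 (assumed) | 12.2 | 1.224 | 7.7% | 9.6% |
| 0.02 (assumed) | 15.33 | 1.287 | 8.4% | 11.8% |
| 0.05 (assumed) | 12.2 | 1.560 | 11.7% | 19.9% |
| 0.05 (assumed) | 15.33 | 1.716 | 13.5% | 23.7% |

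**Check by simulation.** 40,000 null trials per setting, 24 clusters of 15, normal data:

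| ICC | Plain t-test | t-test on cluster means |
|---|---|---|
| 0.01 | 6.7% | 5.0% |
| 0.02 | 8.2% | 4.9% |
| 0.05 | 13.5% | 5.1% |

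A smaller run with skewed data (mean 37, SD 58, as for the primary outcome; 24 clusters of 13; 4,000 replicates) gave 6.1%, 7.9% and 12.7% for the plain test and about 5.0% for the cluster-mean test. Skewness does not change the picture.

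**H1, worst reading only.** Suppose either test could be claimed, with a cluster-mean test standing in for the analysis of covariance. At ICC 0.01 with 15 per cluster, the chance of at least one significant result under the null is about 7.4%, and the two tests disagree in about 3% of null trials.

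**The case against.** Several points can fairly be made for the plan.

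- **The primary analysis already handles clustering.** This stands. The H1 model is cluster-adjusted and the sample size carries a design effect, so the defect lies in the secondary outcomes.
- **The inflation is modest at the only ICC given.** This also stands: 5% becomes 6.3% to 6.7%. That ICC belongs to days of incapacity to work. A reader might infer that the plan's own ICC proves inflation of that size for functional capacity and costs; it does not. The size for H2 and H4 is an assumption, and the higher figures need ICCs that the protocol does not state.
- **The unit of analysis is not stated.** A t-test on cluster summaries is also a two-sided t-test. This is possible but unlikely, because the article mentions cluster adjustment where it is meant, for the H1 model, and nowhere else.
- **A separate analysis plan exists and is not shown.** It could add detail. But the article does not leave the H2 and H4 tests open: it names them, and the named test does not fit the design.
- **H1 does not have two rival verdicts.** A reader might infer that success could be claimed on whichever H1 test is significant. The text does not support this. It ties H1 to the cluster-adjusted analysis of covariance and introduces the t-test only as an addition. What remains is a missing label.

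**Conclusion.** The point holds for H2 and H4: the tests named do not match cluster randomisation or the within-cluster correlation that the sample size assumes. The direction (p-values too small, intervals too narrow) rests on a positive ICC and on t-tests applied to individual patients. The size is about 6.3% to 6.7% instead of 5% if the ICC of 0.01 carries over, and about 8% to 13% for assumed ICCs of 0.02 to 0.05. This should be corrected before analysis, but it does not threaten the primary conclusion. For H1, a clarification is enough.

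**What to change.** - **H2 and H4:** replace the t-tests with a cluster-adjusted model that has a random intercept for MPT month and small-sample degrees of freedom reflecting about 24 clusters. Alternatively, use a two-sided t-test on the cluster summaries and say so.
- **H1:** state that the cluster-adjusted analysis of covariance is the sole confirmatory test. Delete the additional t-test or label it descriptive.

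The change is to wording. It needs no further patients or data, and mixed models can be fitted in SPSS, which the protocol already names. Intervals become wider. At ICC 0.01 and 15.3 per cluster, the design effect adds about 7% (√1.143 = 1.069). A cluster-summary test on 24 − 2 = 22 degrees of freedom adds about 5% more (critical value 2.07 against 1.97), so about 13% in all (1.069 × 1.05 = 1.12 to 1.13). That is the price of holding the stated 5%.

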### Patient and public involvement

No patients were involved in the design and conduct of the study, choice of outcome measures and recruitment to the study. The results of the study will be provided to patients at their request.

## Ethics and dissemination

Ethical and scientific standards in the currently valid version will be taken into account when conducting the study, especially the Memorandum on Good Scientific Practice of the German Research Foundation.^37^ In particular, analysis of secondary data will be performed according to the Good Practice of Secondary Data Analysis guidelines, whereas the primary data collection will be conducted in accordance with the Strengthening the Reporting of Observational Studies in Epidemiology statement.^38^ In addition, the methods of health economic evaluation in health services research and the Hannover Consensus will be applied.^39^ Preliminary to the intervention, a concrete analysis plan is defined. Moreover, the questionnaires developed for the MPT and RP will be pre-tested and all data will be subjected to a validation process. In addition, participation in the intervention is voluntary for the insured, so there is no disadvantage if people do not want to participate. The applied treatments within the intervention and the potential health problems that may occur are known. Possible adverse events include, for example, pain intensification, pain relapse, muscle strain and other side effects that can occur with any physical activity and specific exercises. The practitioners are prepared and educated for possible adverse events. Experienced practitioners will immediately recognise when adverse events occur during the treatment. Moreover, in the case of an adverse event, they will react appropriately, report and document the adverse event in the electronic patient record. Appropriate action will be taken, such as discontinuation or modification of the treatment.

This study has received approval by the ethics committee of the Hannover Medical School (reference number: 8548_BO_S_2019) and is registered at German Clinical Trials Register DRKS00017654. Each participating patient will sign a contract for participation in the programme, and we will obtain written informed consent. Furthermore, all study participants will be comprehensively informed about the use of the collected data and the purpose and procedure of the project. All transmitted data will be pseudonymised and is accessible only to project members. The delivered data will be stored on a secure and encrypted network drive. Access to the files is restricted to the project staff. No data will be passed on to third parties. Furthermore, the information obtained will be used exclusively for research purposes and no information will be passed on that enables conclusions about individual persons. All data collected and processed will be stored on a secure and encrypted hard disk after the end of the study and deleted 10 years after (by 31 March 2033 at the latest).

The study results will be disseminated in national and international journals and conference presentations. The Innovation Fund (G-BA) will publish the study outcomes in a results report. Additionally, the health insurance fund AOK Lower Saxony will make the results available via its homepage and member journals.
